## Abstract

**Background:**

Uterine leiomyomas (often referred to as fibroids or myomas) are common benign, hormone-dependent tumors that grow in the uterus and occur in approximately 25% of reproductive age women, depending on selected population. Treatment recommendation is typically based on fibroid size, location, the patient’s age, reproductive plans, and obstetrical history. Despite the range of treatment options available for uterine fibroids and their symptoms, including hysterectomy, myomectomy, endometrial ablation, endometrial uterine artery embolization, and magnetic resonance-guided focused-ultrasound surgery, myomectomy remains the gold standard treatment for patients who desire fertility-preserving surgery for their uterine fibroids. Myomectomy, while a prevalent surgical option for the removal of fibroids, carries known risks such as fibroid recurrence, symptom recurrence, and the subsequent need for reintervention. Despite ongoing research and advances in medical treatments for fibroids, there currently are no universally recommended therapeutic interventions proven to effectively delay the recurrence of fibroids or the return of symptoms following this procedure. This situation underscores a significant area of unmet medical need and highlights the importance of continued investigation into preventive strategies and long-term management options for patients undergoing fibroid removal with uterine preservation. We designed a study to assess the efficacy of the new FDA-approved GnRH antagonist, Myfembree in delaying the return of fibroids and their associated symptoms.

**Methods:**

A randomized, prospective, open-label clinical trial. The participants (n = 136) will be randomly distributed into two groups. The Control Group (Standard of care) will receive treatment with standard of care (SoC) after surgical myomectomy and the treatment group will receive Relugolix combination therapy (Myfembree®) after surgical myomectomy. The study protocol was approved by the University of Chicago’s Institutional Review Board (IRB#22–0282), ensuring that all participants would provide written informed consent before their inclusion.

**Discussion:**

In this project, we propose the use of daily dosed Relugolix combination therapy (Relugolix with estradiol and norethindrone acetate), which is approved for uterine fibroids treatment, has the potential to delay the recurrence of fibroid symptoms, prolong the improved quality of life and delay need for re-intervention after uterine sparing surgery.

**Trial registration:**

The study protocol was approved by the Institutional Review Board of the University of Chicago on 9/16/2022 and was registered at ClinicalTrials.gov with number NCT05538689 on Sep 7, 2022. All subjects will provide informed consent to participate.

## Introduction

Uterine leiomyomas (often referred to as fibroids or myomas) are common benign, hormone-dependent tumors that grow in the uterus and occur in approximately 25% of women of reproductive age, depending on selected population. While most uterine fibroids are asymptomatic, approximately 25% of women with fibroids develop symptoms requiring treatment [1]. The most problematic symptom for women with uterine fibroids is abnormal uterine bleeding (AUB), with menstrual periods of increased duration and volume [2].

Persistent AUB can induce iron-deficiency anemia and associated fatigue and loss of energy. AUB is a primary reason for the deterioration in the health-related quality of life assessed in patients with uterine fibroids and is a major cause of elective hysterectomy. Other symptoms include bulk symptoms, such as pain or pressure in the abdomen and pelvis due to large myoma(s), low back pain, urinary frequency or urinary tract obstruction, constipation, and adverse perinatal outcomes [3].

The type of treatment recommended for uterine fibroids typically depends upon their size, location, the patient’s age, reproductive plans, and obstetrical history. The decided approach points to the important role of individually tailored therapy. Until recently, only a few medical options were available for women with AUB. Most of the medical therapies produce temporary reduction in both uterine size and fibroid symptoms. A 2016 Cochrane systematic review on surgery versus medical therapy for heavy menstrual bleeding (HMB) showed that 59% of women randomized to the oral medication group had had surgery within two years and 77% within five years [4].

As a direct result of this, the current mainstay of treatment for women with AUB is surgery. Several surgical procedures are frequently performed including hysterectomy, myomectomy by various techniques, endometrial ablation, endometrial uterine artery embolization, and magnetic resonance-guided focused-ultrasound surgery. Each of these options has risks and benefits which must be carefully considered by both provider and patient in a shared decision-making process.

In 2020, a new drug–Oriahnn™, a non-peptide gonadotropin-releasing hormone (GnRH) hormone antagonist ‐ Elagolix combined with estradiol and norethindrone acetate, received US Food and Drug Administration (FDA) approval for the management of AUB-L for up to 24 months. Even more recently, in 2021, relugolix combination therapy (relugolix with estradiol and norethindrone acetate, Myfembree®) received FDA approval for AUB-L in premenopausal women, for up to two years [3]. According to available data Myfembree®, outperformed its placebo comparison groups with a total of 73% and 71% of study participants receiving relugolix combination therapy as compared to 19% and 15% of those in placebo groups, respectively, achieving the primary efficacy endpoint ‐ volume of menstrual blood loss <80 ml and a ≥50% reduction in volume from baseline. Patients receiving Myfembree® versus placebo also showed significant improvements in six of seven key secondary endpoints ‐ measures of menstrual blood loss (including amenorrhea), pain, distress from bleeding and pelvic discomfort, anemia, and uterine volume, but not fibroid volume. These long-term, well-tolerated medical therapies are the first group of medications designed specifically for AUB-L and represent a changing paradigm in fibroid treatment. Of critical note is that unlike with Elagolix combination therapy, Oriahnn™, the use of Relugolix combination therapy, Myfembree® significantly reduced fibroid-related pain measured with the use of a daily electronic diary and a validated pain-outcome measure [3].

Management of symptomatic uterine fibroids often requires a combination of treatment options to achieve desired outcomes. These options may include medical–hormonal, antifibrinolytics, non-steroid anti-inflammatory drugs (NSAIDs); procedural–uterine fibroid embolization, high-intensity focused ultrasound (HIFU) ablation, radiofrequency ablation (RFA) and surgical–myomectomy or hysterectomy. For patients who opt for surgical treatment, they must choose between uterine preservation and definitive surgery i.e., hysterectomy. Myomectomy is the only uterine-sparing surgical treatment of fibroid in which the fibroid is surgically excised from the uterus. Myomectomy is the recommended option for women with large and bulky fibroids who want to retain the option for future fertility or have strong personal or cultural reasons to retain their uterus. It is important to understand that the goal of a myomectomy is not to excise all fibroids but to strategically excise the fibroids that are clinically relevant based on size and/or location. As a result, women who undergo myomectomy, have a known risk of symptom recurrence and subsequent need for reintervention [5].

There are two main proposed theories to explain fibroid recurrence after myomectomy. 1. The growth of small residual fibroids that were strategically retained within the uterus at the time of initial myomectomy [6]. 2. The natural evolution of fibroid-adjacent myometrium leading to initiation and continued proliferation of fibroids [6]. A retrospective cohort study of over 35,000 women undergoing myomectomy, endometrial ablation, and uterine artery ablation showed a 24-month reintervention rate of 4.2% and a 5-year reintervention rate of 19% (17%, 28%, and 20% for abdominal, hysteroscopic, laparoscopic approach, respectively) [7]. In 2001, Rossetti et al., in a study comparing the risk of symptom recurrence after laparoscopic versus abdominal myomectomy, reported a crude rate of recurrence of 27%, and most recurrences were detected by sonography between 10 and 30 months postoperatively [8]. Meanwhile, Nezhat et al. reported a cumulative risk of recurrence of 10.6% after 1 year, 31.7% after 3 years, and 51.4% after 5 years [9]. In a 2020 study comparing the long-term symptom alleviation and re-intervention after HIFU ablation and secondary myomectomy for women with recurrent symptomatic uterine fibroids following myomectomy, the cumulative risk for re-intervention after secondary myomectomy was 3.2% at 1 year and 11.9% at 3 years [10]. Clinical factors that reportedly impact the risk of reoperation after laparoscopic myomectomy due to leiomyoma recurrence include age, number and size of fibroids, size of uterus, type of surgery, parity after myomectomy and use of medical therapies such as GnRH analogs [11]. Fibroid recurrence after laparoscopic myomectomy may be assessed by a) evaluating clinical signs or symptoms, b) screening ultrasound investigation, c) self-reported symptoms based on questionnaires d) focused ultrasound investigation based on clinical exam [12].

Despite the risk of recurrent symptoms and the need for reintervention which is reported by some authors to be as high as 60% after 5 years [13], there have been no clinical trials investigating agents to minimize this risk. As a result, there are no clear recommendations on methods to delay the recurrence of symptoms, growth of additional fibroids, and ensure a sustained improvement in quality of life.

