
### Randomization

Randomization will be prepared by the study statistician using computer-generated random numbers and the method of permuted blocks. It will be implemented using the REDCap randomization module with varying blocks of size 4, 6, and 8 (in a random order) [14]. No one other than the statistician will have access to the sequence of block sizes. Eligible patients will be assigned to one of the following arms:

Arm 1: Treatment with Relugolix combination therapy (Myfembree®) after surgical myomectomy.Arm 2: Treatment with standard of care (SoC) after surgical myomectomy.

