### Sample size and statistical analysis

Data analysis and statistical support is obtained through the Biostatistics Laboratory (located within the Department of Public Health Sciences) at the University of Chicago. The primary endpoint of this study will be a composite endpoint defined as the occurrence of any of the following three component endpoints over a 24 month follow up period.

Endpoint 1 (Fibroid Recurrence)

Endpoint 2 (Symptom Recurrence)

Endpoint 3 (Need for Re-intervention)

A Chi-square test will be used to compare the rate of occurrence of the primary endpoint in the two treatment arms.

Assumptions regarding the frequency of endpoint 1 are based on ref [8]. That study observed 23% recurrences in the abdominal group and 27% in the laparoscopic group over 40 months. 84% of these recurrences were seen within 24 months. Therefore, we assume the recurrence rate among patients with laparoscopic or abdominal surgery over 24-month follow-up time in the control arm will be (23%+27%)/2*0.84 = 21%. We assume a recurrence rate of 5% in the treatment group (i.e., effect size of 16% absolute reduction). For endpoint 2, a symptom recurrence rate of 7.6% in the control group [16], and 1.5% in the treatment group are assumed. For endpoint 3, a reintervention rate of 14.4% [16] in the control group and 3% in the treatment group are assumed. Assuming endpoint 1 is independent of endpoints 2 and 3, and a correlation of 0.5 between the endpoints 2 and 3, leads to a rate of 33.8% for our primary composite endpoint in the control arm vs. 8.25% in the treatment group. A sample size of 94 patients (47 per arm) will provide 80% power to detect a difference of this magnitude at a two-sided alpha level of 0.05 (PASS, Kaysville, Utah) utilizing the chi-square test as the statistical testing method. To allow for a 30% dropout rate, the sample size will be increased to 136 patients. It is expected that the 136 patients will be accrued during the first year of the trial (10–12 per month) with two years of follow-up after the last patient is enrolled. The number needed to treat (NNT) will be calculated as the reciprocal of the difference in observed event rates along with a 95% confidence interval. While the sample size has been increased to allow for a 30% dropout rate, every effort will be made to retain subjects in the trial and to obtain outcome data. Sensitivity analyses will be performed to examine the effects of dropouts on the results.

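### The primary 24-month comparison uses no baseline information; prespecified adjustment for residual fibroids and age would be a modest efficiency gain

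*Protocol article*

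**What the plan says.** On the primary analysis, the section Sample size and statistical analysis of the protocol article is definite: "A Chi-square test will be used to compare the rate of occurrence of the primary endpoint in the two treatment arms". The number needed to treat is the reciprocal of the difference in observed event rates. The only sensitivity analyses mentioned concern dropout, and models are planned only for pain and quality-of-life scores over time.

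On allocation, the Randomization section says: "Randomization will be prepared by the study statistician using computer-generated random numbers and the method of permuted blocks". Block sizes are 4, 6 and 8, and no stratification factor is named.

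On prognosis, the Introduction gives growth of small fibroids left in place at surgery as one of two theories of recurrence, and explains that myomectomy does not aim to remove every fibroid. It adds that the factors reported to affect reoperation after laparoscopic myomectomy "include age, number and size of fibroids, size of uterus, type of surgery, parity after myomectomy", together with medical therapy. It also cites five-year reintervention by route: "17%, 28%, and 20% for abdominal, hysteroscopic, laparoscopic approach, respectively".

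**The concern.** The article argues that women differ in their risk of recurrence or reoperation from the outset, and then fixes a primary comparison that uses none of this. If a baseline variable predicts the composite, adjusting for it narrows the interval around the risk difference at no cost in patients, and removes the part of the observed difference that comes from a chance imbalance in that variable.

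The information should largely be at hand. A scan at weeks 4–6 is required of every participant. Recurrence counts only if a fibroid is new relative to that scan, so someone has to read which fibroids were present. Age is checked at eligibility. At stake is some precision in a small trial, and protection against choosing covariates after the results are seen in an open-label study.

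**Working it through.** **1. The plan's own figures.** Inputs (Sample size and statistical analysis): component rates of 21%, 7.6% and 14.4% on control and 5%, 1.5% and 3% on treatment; correlation 0.5 between components 2 and 3; component 1 independent of both.

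- Control: P(2 and 3) = 0.076×0.144 + 0.5×√(0.076×0.924×0.144×0.856) = 0.0575. P(2 or 3) = 0.220 − 0.0575 = 0.1625. Composite = 1 − 0.79×0.8375 = 33.8%.
- Treatment, same steps: P(2 and 3) = 0.0108, P(2 or 3) = 0.0342, composite = 1 − 0.95×0.9658 = 8.25%.

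Both match: "leads to a rate of 33.8% for our primary composite endpoint in the control arm vs. 8.25% in the treatment group". At two-sided 5% and 80% power, the two-proportion formula gives 39 per arm without and 47 per arm with continuity correction. The stated 47 is the corrected figure, and 47/0.7 = 67.1 rounds up to 68 per arm, or 136. The chi-square test without correction has about 87% power at 47 per arm (normal approximation) or 89% (exact). The planned power therefore does not rely on adjustment.

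**2. Expected events.** At 47 per arm: 47×0.338 = 15.9 and 47×0.0825 = 3.9, together about 20. At 68 per arm: 23.0 and 5.6, together about 29.

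**3. Chance imbalance.** For a factor present in half the women (assumption), the SD of the difference in prevalence between arms is √(2×0.25/n): 10.3 points at n = 47 and 8.6 points at n = 68. A difference above 10 points has probability 33% and 24% respectively; above 20 points, 5% and 2%.

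**4. Surgical route, the only factor with figures.** The shift in the risk difference is imbalance × risk contrast. With two equally common routes, the share of variance explained is 0.25×(contrast)² / [p̄(1−p̄)].

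| Contrast | Shift at a 20-point imbalance | Variance explained |
|---|---|---|
| 17% vs 20% (5-year reintervention) | 0.6 points | 0.1% |
| 23% vs 27% (40-month recurrence) | 0.8 points | 0.2% |
| 17% vs 28% (5-year reintervention) | 2.2 points | 1.7% |

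The planned difference is 33.8 − 8.25 = 25.6 points. A factor separating 20% from 50% risk (assumption) would shift the result by 6 points at the same imbalance.

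**5. Gain from a stronger covariate.** The article gives no strength for residual fibroids or age, so the odds ratio (OR) per SD is assumed over a range. Simulation: 4,000 trials per setting, one standard normal covariate, marginal rates held at 33.8% and 8.25%. Power compares the chi-square test with a covariate-adjusted logistic score test at 47 per arm. Variance reduction is for a linearly adjusted risk difference, at 47 and 68 per arm.

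| Assumed OR per SD | Power, unadjusted | Power, adjusted | Variance reduction |
|---|---|---|---|
| 1.35 | 89.2% | 89.6% | 0–1% |
| 1.65 | 89.6% | 90.1% | 2–3% |
| 2.2 | 89.0% | 91.6% | 6–8% |
| 2.7 | 88.8% | 92.8% | 11–12% |
| 4.5 | 89.1% | 94.8% | 15–16% |

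At 68 per arm, power is about 97% unadjusted and 97–99% adjusted. Under no effect, the unadjusted test rejects in 4.5–6.2% of trials.

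As a rough guide for a yes/no factor in half the women, the SD is 0.5, so the OR between groups is about the square of the OR per SD: 1.65² = 2.7 and 2.2² = 4.8. Residual fibroids would have to be a strong predictor before the gain exceeds a few per cent.

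**The case against.** The strongest reply is that nothing here is wrong. After randomisation an unadjusted chi-square test is valid, chance imbalance is already allowed for in the type I error and the confidence interval, and the planned power is exceeded without adjustment. All of that stands. A reader might infer that the result would be biased or uncorrectable if the arms differed on a prognostic factor; the documents and the calculations do not support that.

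A reader might also infer that surgical route ought to be a stratum or covariate, because the article quotes different reintervention rates by route. Its own figures make the effect negligible. That the planning rate is stated for particular routes ("we assume the recurrence rate among patients with laparoscopic or abdominal surgery over 24-month follow-up time") concerns the sample-size assumption, not adjustment. Recruitment began in February 2023, so stratifying now is no remedy.

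Three further cautions stand. The list of factors concerns reoperation after laparoscopic myomectomy, not the composite, and carries no effect sizes. The article does not say that route or fibroid count is recorded as a data item, so it cannot be claimed that the covariates are already collected. And a Cox model would replace the 24-month risk difference with a hazard ratio, although ultrasound recurrence is seen only at six-monthly scans.

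The reply does not remove the point altogether. The primary test is a stated choice rather than a detail left open, and a better-informed comparison of the same 24-month risk is available. A statistical analysis plan that already contains one would close the point.

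**Conclusion.** The concern holds as a modest efficiency point. The primary comparison ignores baseline variables that the article itself regards as relevant, and a short prespecified adjustment would serve the same question slightly better. The size is uncertain: close to nothing if residual fibroids and age are weak predictors, a 6–12% reduction in variance at an assumed odds ratio of 2.2–2.7 per SD, and about 15% only for a very strong predictor. Any single figure for the gain would rest on an assumption the documents do not supply. The sample size and the validity of the planned test are not in question.

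**What to change.** Before outcome data are examined, prespecify a comparison of the 24-month composite adjusted for two baseline variables: presence of residual fibroids on the weeks 4–6 ultrasound, and age. Use logistic regression and report the standardised risk difference, that is, each woman's predicted risk under each arm, averaged over all women and subtracted. The number needed to treat can be derived from it. Report the unadjusted chi-square test alongside, and state in advance which of the two carries the conclusion.

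Confirm first that residual-fibroid status is recorded as a data item for every woman, and that the scan precedes the first dose; the text calls the scan baseline but does not spell out the order of scan, randomisation and dispensing. Later parity, which the article also lists, arises after surgery and should not be a covariate.

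The cost is analysis wording and possibly one data field. The downside is sparse data: with about 4–6 events expected on treatment, the list must stay at two covariates, and a fallback such as Firth penalisation should be named, with an intercept correction because plain Firth estimates distort predicted risks.

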## Methods

### Study design and location

This will be a randomized, single-center, open-label interventional clinical trial of treatment with Relugolix combination therapy (Myfembree®) after surgical myomectomy vs. Treatment with standard of care after surgical myomectomy. The standard of care will depend on the type of surgery, health history, and clinical symptoms. It often includes pain management, bleeding management, physical exams, and pelvic ultrasound. The recruitment will be from the University of Chicago Medical Center in Illinois USA. The randomization scheme will be coordinated by the Biostatistics Laboratory (located within the Department of Public Health Sciences) at the University of Chicago. The study protocol was approved by the Institutional Review Board of the University of Chicago on 9/16/2022 (IRB22-0282) and the initial recruitment of participants commenced on February 2, 2023, with a written consent form being obtained from each participant. The study is anticipated to conclude in February 2026.

Fig 1 summarizes the study design.

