### Variables

The primary outcome will be a composite outcome including:

Fibroid recurrence when compared to the post-myomectomy baseline pelvic ultrasound (transvaginal and/or transabdominal), defined as a new fibroid identified on ultrasound with volume >1 cm3 [8]Symptom recurrence defined as either of the following:I. Moderate to heavy menses with PBAC score ≥ 120 for patients with pre-operative heavy mensesII. Pelvic pain during menses as measured on the Numerical Rating Scale NRS ≥ 4 at baselineIII. Score ≥ 25 on the symptom severity scale.Need for reintervention defined as need to undergo a procedure or surgery for treatment of uterine fibroids including repeat myomectomy, uterine fibroid embolization, radiofrequency ablation or hysterectomy.

The secondary outcomes will include:

Fibroid recurrence, compared to baseline pelvic ultrasound (transvaginal and/or transabdominal), defined as a new fibroid identified on ultrasound with volume >1 cm3.Return of moderate to heavy menses defined as PBAC score ≥ 120 for patients with pre-operative moderate to heavy menses.Need for reintervention defined as need to undergo a procedure or surgery for treatment of uterine fibroids including repeat myomectomy, uterine fibroid embolization, and radiofrequency ablation.Time to event (procedure or surgery) such as radiofrequency ablation (RFA), myomectomy, hysterectomy, or uterine fibroid embolization (UFE).Symptom recurrence according to the UF quality of life symptoms severity subscale and Bleeding & pelvic discomfort (BPD) scale.Return of pelvic pain during menses as measured on NRS [15]Quality of life as measured by Patient Reported Outcome and Quality of life questionnaires (UFS-QOL, WPAI:SHP, Female Sexual Function Index)

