### Intervention

At 4–6 weeks post-surgery, participants will complete a baseline ultrasound. Participants in the medication arm will receive a once-daily pill that contains Relugolix (a gonadotropin-releasing hormone antagonist), estradiol (an estrogen), and norethindrone acetate (a progestin). Myfembree will be dispensed after randomization at study visit 1. Pill counts and checks will be completed at each visit. A total of 10 visits are necessary including the screening visit.

All participants will be asked to fill out questionnaires at baseline and then every 3 months. The questionnaires will be filled by paper or electronically using uMotif e-diary.

Uterine Fibroid Symptom and Health-Related Quality of Life (UFS-QoL) fibroid QuestionnaireWork Productivity and Activity Impairment Questionnaire: Specific Health Problem V2.0 (WPAI:SHP)Female Sexual Function Index (FSFI)

All participants will be asked to fill a set of diaries at baseline and daily for the study duration.

Daily electronic diaries (eDiary) to measure compliance with study treatmentMenstrual bleeding diaryRecord of use of feminine products for menstrual bleedingPictorial bleeding assessment chart (PBAC) scoresPelvic pain during menses by the numeric rating scale (NRS)Use of pain medication to treat pain caused by uterine fibroids

Participants will have access to all questionnaires once they are enrolled in the study and they will be accessible anywhere through their phones, mobile, or computer devices.

All participants will undergo pelvic ultrasounds at the following time periods:

Week 4–6: post-myomectomy baseline ultrasound (transvaginal and/or transabdominal)Month 6: pelvic ultrasound (transvaginal and/or transabdominal)Month 12: pelvic ultrasound (transvaginal and/or transabdominal)Month 18: pelvic ultrasound (transvaginal and/or transabdominal)Month 24: pelvic ultrasound (transvaginal and/or transabdominal)

All participants will have blood work performed every 6 months or at clinically indicated intervals:

Cell Blood Count (CBC)Complete Metabolic Panel (CMP)Urine pregnancy test during each clinic/in-person visit.

Please refer to Fig 2 for a detailed study timeline & interventions.

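### Endpoint 1, the largest component of the primary composite, rests on judging a fibroid as new on ultrasound in an open-label trial, and the article describes no masking of the reader

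*Protocol article*

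**What the plan says.** Under Study design and location the article says: "This will be a randomized, single-center, open-label interventional clinical trial". Under Variables, the first component of the primary composite is fibroid recurrence relative to the post-myomectomy scan, "defined as a new fibroid identified on ultrasound with volume >1 cm3". The Intervention section sets the schedule ("All participants will undergo pelvic ultrasounds at the following time periods"): a baseline scan at weeks 4–6, then follow-up scans at months 6, 12, 18 and 24, each transvaginal and/or transabdominal. It does not say who reads them or what the reader knows.

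The one concealment measure described is under Randomization: "No one other than the statistician will have access to the sequence of block sizes". That protects allocation, not the reading of outcomes.

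The Introduction explains that "the goal of a myomectomy is not to excise all fibroids but to strategically excise the fibroids that are clinically relevant", and it names growth of small retained fibroids as one of two routes to recurrence.

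Sample size and statistical analysis assumes endpoint 1 in 21% of controls. For the drug arm it says: "We assume a recurrence rate of 5% in the treatment group". The composite is compared between arms by a chi-square test.

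**The concern.** If fibroids are left in the uterus on purpose, the follow-up reader has to decide whether a lesion is new or was already there, and whether it exceeds 1 cm3. The size threshold and the baseline scan limit that discretion but do not remove it. A reader who knows the arm may call more new fibroids in controls or fewer on drug. Each woman has four follow-up scans, and one positive call on any of them makes her a primary event.

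The composite cannot separate such a difference in reading from efficacy. The sensitivity analyses that the article mentions address dropout, so they would neither detect nor correct it. What is at stake is the interpretation of the primary comparison, because this component is expected to supply a large part of it.

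**Working it through.** **Inputs** (Sample size and statistical analysis), control vs drug:
- endpoint 1 (ultrasound): 21% vs 5%
- endpoint 2 (symptoms): 7.6% vs 1.5%
- endpoint 3 (re-intervention): 14.4% vs 3%
- endpoint 1 independent of the others; correlation 0.5 between endpoints 2 and 3
- 47 per arm evaluable, 68 per arm enrolled (136/2), two-sided alpha 0.05.

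**Step 1. Reproduce the plan's composite.**
- p23 = p2·p3 + 0.5·√(p2(1−p2)·p3(1−p3)); endpoint 2 or 3: u = p2 + p3 − p23; composite = 1 − (1−p1)(1−u).
- Control: p23 = 0.0575; u = 0.076 + 0.144 − 0.0575 = 0.1625; composite = 1 − 0.79 × 0.8375 = 0.338.
- Drug: p23 = 0.0108; u = 0.015 + 0.03 − 0.0108 = 0.0342; composite = 1 − 0.95 × 0.9658 = 0.0825.

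Both match the stated 33.8% and 8.25%. The planned difference is 25.6 points.

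**Step 2. How much rests on ultrasound.**
- Added to the control composite beyond endpoints 2 and 3: 33.8 − 16.3 = about 17.6 points (unrounded 33.84 − 16.25).
- Planned difference without ultrasound: 16.25 − 3.42 = 12.8 points, so ultrasound carries 25.6 − 12.8 = 12.8 points, about half.
- If the drug left the ultrasound component unchanged and it stayed in the composite, the drug rate would be 1 − 0.79 × 0.9658 = 0.237. The difference would be 10.1 points and power at 47 per arm about 19%.

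**Step 3. Illustration of reading bias with no true drug effect.** The documents give no bias sizes; the ranges are assumptions. Both arms have the control rates. Rejection probability is from the two-sided normal approximation with pooled variance.

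*Spurious calls in controls only, 3–5% per scan, independent across four scans:*
- Per woman: 1 − 0.97⁴ = 0.115; 1 − 0.95⁴ = 0.185.
- Added to the composite: × (1 − 0.338) = 0.076 and 0.123, about 8–12 points.
- Rejection: about 12–23% at 47 per arm and 15–31% at 68 per arm, against a nominal 5%.

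*Under-calling on drug only, 10–20% of ultrasound recurrences:*
- Difference: 0.21 × s × (1 − 0.1625) = 0.018 (s = 0.10) and 0.035 (s = 0.20), about 2–4 points.
- Rejection: about 5.4–6.5% at 47 per arm and 5.5–7.2% at 68 per arm, close to nominal.

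*Upper limit of under-calling alone:* missing every ultrasound recurrence on drug gives 33.8% vs 16.3%, or 17.6 points, short of the planned 25.6.

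**The case against.** **The article is silent; it does not say that readers know the arm.** This stands. Open-label treatment is compatible with masked reading, the full protocol is not shown, and the two design figures are missing from the text reviewed. A reader might infer that the scans are read unmasked; the documents do not establish that. Still, who is masked is a basic design item. The article declares the trial open-label, defines the endpoint and sets out the schedule without exempting the reader.

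**Ultrasound is not the only component that could be protected.** Also right. Re-intervention is defined by named procedures, so whether one took place, and for fibroids, could be adjudicated without the arm, although the decision to operate cannot be masked. Conversely, a masked ultrasound reader does nothing for the patient-reported bleeding, pain and symptom scores.

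**It is tempting to say that ultrasound supplies 21 of the 33.8 control points.** It does not, because the components overlap. Its addition is about 17.6 points.

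**The bias sizes are assumed, and the larger ones are demanding.** True. Spurious calls of 3–5% per scan mean that about 30–41% of all new-fibroid calls in controls would be false (0.79 × 0.115 = 0.091 of 0.301, up to 0.79 × 0.185 = 0.146 of 0.356), despite a size threshold and a recorded baseline scan. The under-calling scenario barely moves the error rate. The figures show sensitivity; they do not estimate what will happen.

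**Conclusion.** The point holds as a design weakness that should be closed. Followed as written, the plan leaves its largest assumed primary component open to differential reading that no described analysis would correct. The component matters: about 17.6 of the 33.8 control points and about half of the planned 25.6-point difference, both resting on the plan's own rates and its independence assumption.

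A reader might go further and conclude that reading bias could produce the whole planned effect. The figures do not support that. Under the assumed ranges the false difference is about 8–12 points from over-calling in controls or about 2–4 points from under-calling on drug, and under-calling alone cannot exceed 17.6 points. Bias can mimic part of the effect and inflate the false-positive rate; how far depends on bias sizes that the documents do not give. The sample size is not in error on this account. Confidence is medium, because the full protocol may already provide for masked reading.

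**What to change.** Unless the full protocol already provides it, state that study scans are performed and reported by the existing imaging staff without knowledge of the arm. That means no arm on the order or worklist, and comparison only with the post-operative baseline scan. Use that report to decide endpoint 1, starting with the next scans. If masked reading is already in place, one sentence saying so settles the point.

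The cost is an instruction to the imaging service, with no extra scan, reader or patient and no change to the sample size.

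It has limits:
- Recruitment began in February 2023, so scans already reported are not covered.
- Some readers may see the arm in the medical record or infer it; the Introduction reports effects of the drug on amenorrhea and uterine volume.
- The patient-reported symptoms and the decision to re-intervene remain open to knowledge of treatment.
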